## Abstract

**Background:**

The high psychological burden of rape, together with complications such as pregnancy and chronic conditions, is associated with an increase in mental disorders. Social cognitive theory (SCT) is an important health theory that views behavior as dynamic and influenced by environmental, behavioral and individual factors. The aim of the present research is to determine the effect of an educational intervention on post-traumatic stress disorder and social cognitive theory constructs in women who have experienced sexual assault.

**Methods/design:**

This study is randomized, double-blind clinical trial research that will be conducted on 40 women with experience of sexual. In this research, by the intervention program based on social cognitive theory include" awareness, self-efficacy, outcome expectations and environment. Written consent will be obtained from the participants to participate in the research. Participants in the intervention group will be taught about health, hygiene, psychology and stress reduction methods in group or individual sessions according to their preference in 6 sessions of 60 min each, one session per week. A post-test will be conducted for both groups.

**Discussion:**

This study provides comprehensive data on the effect of providing an educational intervention using the social cognition Theory. Social cognitive theory focuses on how patterns of behavior are learned and how they function in interaction between the individual and the environment. It seems that the use of this theory in designing the content of educational interventions can be useful and practical.

*Trial registration*: The trial is prospectively recorded at the IRCT registry (Trial ID: IRCT20230926059526N1. Date recorded: 18/10/2023.

## Introduction

Sexual assault against women is an important public health and human rights issue with heterogeneous prevalence around the world [1]. Social inequalities and the cultural structures of societies play a role in the creation, perpetuation and survival of this issue [2]. Although the formation provided by virtual campaigns and the sharing of victims' experiences has increased public awareness of the problems and complications of sexual assault in recent years [3], in countries such as Iran, victims experience a very high psychological and social burden. This is because these individuals are not only the victims of an act of violence, but also bear the social pressure caused by the taboo of sexual assault taboo in society. In many cases, these victims do not report the assault to legal and health authorities and are therefore deprived of sexual health preventive measures. There are no clear and official statistics and information on sexual assault and physical abuse in Iran. More than 80% of cases of sexual harassment go unreported and the real statistics are higher than the published statistics [4]. According to the National Sexual Violence Resource Center, one in five American women will experience sexual assault at some point in her life [5]. Khoramin et al. indicated in a study that the prevalence of post-traumatic stress disorder in rape victims referred to forensic medicine in Kohgiluyeh and Boyar Ahmad provinces was almost 92% [6]. The results of the research on post-traumatic stress disorder among those referred to forensic centers in Tehran indicated that the rate of post-traumatic stress disorder and the rate of depression were respectively, 61.6% and 47.7% among the survivors [7]. The high psychological burden of rape, together with complications such as pregnancy and chronic conditions such as chronic pelvic pain, is associated with an increase in mental disorders. In cases where women have experienced more severe assaults, they show more symptoms of psychological distress [8]. Therefore, sexual assault as a crisis-causing event is associated with post-traumatic stress disorder, a complication that hinders the follow-up of diagnostic and therapeutic measures in victims [9]. In addition to the disturbed mental state of the victims, other factors also fuel this problem. Research has shown that there is a low level of awareness of sexually transmitted infections among the rape survivors attending the forensic medical centers. Based on the results of this study, 59% of the participants had no knowledge of the nature, mode of transmission and prevention of sexually transmitted infections, and 24% had low knowledge [10]. These findings show that rape victims in Iran are mostly unaware of the dangers of rape and may not take health-related measures despite the high post-traumatic stress they experience due to the social pressure caused by the taboo of being a rape victim. The interactions of individuals with the legal, medical and healthcare systems and the search for help after an accident have an impact on their mental well-being. Seeking help after the sexual assault is described by victims as a second rape, and many of these victims do not receive comprehensive care [11, 12]. Given the high economic and social burden of sexual assault on individuals and society, it is recommended that guidelines for accessing essential medical, legal, social support and reporting services be provided and established [1, 2]. To prevent post-traumatic stress disorder in 10 women who had recently been sexually assaulted, Fao et al. in a study designed a comparative program between an intervention group that received a cognitive-behavioral program and a control group that underwent an assessment of trauma-related psychological pathology. The results indicated that two months after the rape, women in the intervention group had fewer symptoms of post-traumatic stress disorder, and after five and a half months, the intervention group had less depression than the control group [13]. Other studies have used various methods such as client-centered therapy [14], mental imagery, and reprocessing of nightmares and suicidal thoughts [15] to reduce symptoms of psychological distress and depression in women who have experienced sexual assault. The individual, situational and cultural factors that contribute to the blaming of rape survivors should be considered in the design of studies and interventions [16]. Social Cognitive Theory [SCT] is an important health theory that views behavior as dynamic and influenced by environmental, behavioral and individual factors. Given that rape is a social problem, educational interventions that focus on the interpersonal level, such as those based on social cognitive theory, may be effective in resolving conflicts caused by the psychological pressures of rape on victims. It also appears that the constructs of this theory can be used to change a one's behavior, awareness and ability [17–19]. Investigating the effect of long-term exposure therapy on social support and the symptom severity in patients with post-traumatic stress disorder, Aghmiuni et al. found that the mentioned exposure therapy can alleviate post-traumatic stress disorder [20]. Studies in Western societies have shown that social support is an effective factor in reducing symptoms of post-traumatic stress disorder caused by sexual assault [21–23]. Cultural factors, economic conditions, family situation, existing legal/punitive systems [24] and the different societal views of women who have experienced sexual assault in Western and traditional societies are among the factors that make the impact of social support different. This is because the disclosure of this incident may expose women who have experienced sexual assault in traditional societies to particular social challenges and social stigma, thus questioning the impact of social support on PTSD in traditional societies [25]. Various measures have been taken to reduce the symptoms and severity of post-traumatic stress disorder. However, there is a continuing need for training programs and more research into post-traumatic stress disorder caused by the experience of sexual assault. The reduction of violence against women and its complications and the achievement of gender equality are among the world's development goals. Awareness-raising and training of women is one of the key aspects in achieving this goal. The aim of the present research is to determine the effect of an educational intervention on post-traumatic stress disorder and social cognitive theory constructs in women who have experienced sexual assault. In case of appropriate impact, the study can be used as an intervention to reduce individual and social complications, and economic costs. It can also promote health behavior change and the management of post-traumatic stress disorder, and encourage healthcare-seeking, thereby improving the quality of life of women who have been raped. This study determines and compares the background characteristics and the mean scores of post-traumatic stress, awareness, health-related attitudes and behaviors, perceived social support, and self-efficacy in and between two intervention and control groups before and two months after the intervention.

## Methods/design

The overall aim of the study is to designing and determining the effect of a training program based on social cognitive theory on post-traumatic stress disorder in women who experienced sexual assault. More specifically we will:

QuestionWhat are the individual characteristics of the research units in the two intervention and control groups?

Aims.Determining and comparing the average score of awareness, attitude and performance of health-related behavior in post-traumatic stress disorder of women who experienced sexual assault between the test and control groups before and two months after the intervention.Determining and comparing the average score of perceived social support in post-traumatic stress disorder in women who experienced sexual assault between the test and control groups before and two months after the intervention.Determining and comparing the average score of self-efficacy in post-traumatic stress disorder in women who experienced sexual assault between the test and control groups before and two months after the intervention.Determining and comparing the average score of post-traumatic stress in women who experienced sexual assault between two test and control groups before and two months after the intervention.

### Study design

This study is randomized, double-blind clinical trial research that will be conducted on 40 women with experience of sexual assault referred to Iran-Isfahan Welfare and Forensic Medicine Centers. In the first phase of the educational intervention, the program, content and questionnaire will be designed and compiled, and in the second phase, sampling will be performed in the form of a census and, then, training sessions will be held. For the purpose of randomization, table of random numbers will be used for two intervention and control groups with a ratio of 1:1. The design of this clinical trial follows the requirements of the CONSORT statement.

#### Participants, recruitment, and study area

The statistical population of the study includes all women who, as a result of experiencing sexual assault, have referred to the Social Emergency and Forensic Medicine Centre of Isfahan City for support and through legal centers related to sexual assault, and whose referrals have been recorded. The study sample consists of women with experience of sexual assault who are referred to social counseling centers and forensic medicine in the city of Isfahan and who meet the conditions to participate in the study. The participants will be contacted using their recorded phone number.

#### Inclusion criteria

Women aged 18–45 years.Women with at least one experience of sexual assault with an interval of at least one month from the incident [if there are symptoms of the disorder, no maximum], and obtained a score of 33 and above in PCL-5 questionnaire with the ability to diagnose based on the DSM-5 diagnostic system and the PTSD was confirmed in them by a clinical psychologist.No current drug use.No current major brain disease.No mental retardation.No major psychiatric disorder.No treatment process.No psychiatric history.No psychiatric record [psychotic disorders: psychosis, bipolar disorder, schizophrenia, bipolar I disorder with psychotic symptoms, dementia], and no pregnancy at study entry.

#### Exclusion criteria

Missing more than one training session.Experiencing another crisis during the study [mourning the death of a loved one, pregnancy, bankruptcy of the loved ones] were the exclusion criteria.

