#### Second phase: implementation of the intervention and training sessions

The instructor is a Master of Forensic Midwifery student and all training is delivered under the supervision and approval of the research team and the research team's clinical psychologist, and the content is approved by the research team. Participants in the intervention group will be taught about health, hygiene, psychology and stress reduction methods in group or individual sessions according to their preference in 6 sessions of 60 min each, one session per week. After obtaining the ethics permission from Isfahan University of Medical Sciences and the IRCT code, a letter of introduction is obtained to be submitted to Isfahan Welfare and Forensic Medicine Organizations. Written permission will be obtained from the officials to enter and access the medical files, and the researcher will be present in the research environment and introduced to the officials. The objectives of the research and the method of doing the study will be explained. An educational intervention is designed and developed, taking into account the constructs of social cognitive theory and focusing on health-related behavior. Sampling will take the form of a census of the participants who meet the eligibility criteria after accessing the file in the above-mentioned centers, and they will be invited to participate in the study by telephone. The participants are randomly assigned to the intervention and control groups using a random number table. Before participating in the research, they will be given a description of the research objectives, the intervention method and sufficient assurances of confidentiality, and they will be able to choose whether to participate in group or individual sessions to receive the educational intervention. Written consent will be obtained from the participants to participate in the research, and pre-test will be performed. Participants allocated to the intervention group will be invited to participate in four groups of 5 participants according to their age and education, or if they do not wish to be in a group, they will be invited to attend individual sessions. Then, an educational intervention based on social cognitive theory will be implemented in the Welfare and Forensic Medicine Organizations during 6 sessions of 45–60 min once a week and for 6 weeks by a trained instructor. The qualification of this instructor is confirmed by the consulting professor, [name], [PhD in clinical psychology] during a three-session program with health-related educational content. In order to provide the educational intervention [attached], the student will conduct the intervention based on social cognitive theory constructs in sessions under the supervision and approval of the team psychologist, and two sessions will be carried out in the presence of the professor. The educational content has been prepared on the basis of theoretical constructs and using the scientific techniques available in psychological articles and books, and taking into account the conditions required for the training, and will be analyzed and approved by the supervisor and advisor. In order to make the intervention in the direction of social support and environment, according to the specific social conditions, educational brochures will be given to the individuals to have the influence of the environment, so that they can request social support from the supportive people or give the brochure to their supporters and receive the education indirectly. It should be noted that in parallel with the intervention group, in order to double-blind the control group, a one-hour session for the control group will be provided with the routine training of the above-mentioned centers, without focusing on specific theoretical structures and continuous follow-up of sexually transmitted diseases. During the study, they will use the services and routine care provided by the centers, they will not be deprived of these services, and the researcher will not know about the groups. The time required for the research process [proposal preparation and approval, sampling and intervention, final report and article preparation, article editing and submission] is 14 months. Brochures, booklets and CDs with the same content as the sessions are used as teaching methods to make the sessions more accessible. For two months after the end of the intervention, the participants will be followed up, if necessary, through a telephone line, virtual group and SMS, and their questions will be answered. A post-test will be conducted for both groups to check the effect of the educational intervention two months after the last intervention session in the intervention group. This study is conducted to measure the effect of the independent variable (intervention training) on the dependent variables health-related awareness, health-related attitude and behavior, self-efficacy, perceived social support and PTSD severity score of women with experience of sexual assault. It also aims to reduce the symptoms of stress disorder, increase awareness, and improve health-related attitude and behavior, self-efficacy and perceived social support. The variables of background characteristics, self-efficacy, perceived social support, post-traumatic stress disorder, awareness and health-related attitudes and behaviors will be measured using a self-report questionnaire before and two months after the intervention in two groups. The measurement tools used in this research include a questionnaire on demographic characteristics, a standard questionnaire on self-efficacy, a standard questionnaire on perceived social support, PCL-5 post-traumatic stress disorder questionnaire, and a researcher-made questionnaire on health-related awareness, attitude and behavior. The questionnaire will be filled as self-report, and if a participant is illiterate, it is read out to them. It is hoped that by using the constructs of social cognitive theory in the content of training sessions based on scientific documents, it will be possible to meet the needs of these participants and prevent further injury and problems.

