
### Control group

The control group will continue to receive routine care, plus ongoing training on how to follow up sexually transmitted infections. The routine care that is done in our country is that, if a woman is sexually assaulted, she should first go to the police headquarters. Then the police introduce her to one of the court's branches that deals with rape issues. The judge introduces her to the Forensic Medicine, where the investigation of the raped woman is conducted, and the evidence and documents of the court case are presented, and according to the administrative procedures, they try to reach the rapist. At the same time, if the woman is raped, she will be introduced to a counselor who is present in the court so that she can be consulted and taken care of. Any type of health care (HIV test, prophylactic medication for STI, etc.) is done by raped women in private centers or comprehensive health service centers. Figure 1 details the flow of participants from enrollment until the last follow-up contact for control and intervention subjects.

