### Sample size

According to the mean values and standard deviation before and after the educational intervention in previous studies [26] and asking the opinions of statistics experts and considering α = 0.05 and β = 0.2, the standard deviations of 7.95 and 8.06 in the intervention and control groups, and a minimum difference of 7.5 points between the two groups in terms of post-traumatic stress disorder, the sample size is calculated to be 18 participants in each group. However, considering a drop-out rate of 10%, the sample size is set at 20 participants in each group.

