#### Data collection tools and methods

After the woman is randomized to the control or intervention group and has signed the written consent, having been previously informed of the study aims, the researcher will let her know about the follow-up she will need to complete during the study. The measurement tools used in this research include a questionnaire on demographic characteristics, GSE-10 self-efficacy questionnaire, a questionnaire on perceived social support, PCL-5 post-traumatic stress disorder questionnaire, and a researcher-made questionnaire on health-related awareness, attitude and behavior.

The Demographic Characteristics Questionnaire covers demographic information such as age, economic status, education level, occupation, marital status, number of children if married, spouse's education and occupation, residential status, birth order, parents' education and health insurance status. The number of supporters, number of rapes, previous experience of rape, relationship with the rapist, number of rapists and beatings during the event can be recorded using the researcher-made checklist. For example, "what is your birth order in your family?".

To examine perceived social support, the Multidimensional Perceived Social Support Scale is used, which measures social support from three sources of family, society and friends, using 12 items on a 7-point Likert scale ranging from “strongly disagree” (score 1) to “strongly agree” (score 7). The minimum and maximum scores for a person's perceived social support on the whole scale are 12 and 84, respectively, with the higher the score, the greater the social support. The validity and reliability of the tool has been checked and confirmed by Besha rat [27, 28]. A sample item is "There is a special person in my life who helps me when I need help", and is measured on a 7-point Likert scale.

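### Both exclusion criteria are events after randomisation, and under the one-session control description the attendance rule can remove only intervention women, leaving the comparison open to selection bias

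*Protocol article*

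**What the plan says.** The Exclusion criteria section of the protocol article holds two items. One is "Missing more than one training session". The other is "Experiencing another crisis during the study", with bereavement, pregnancy and bankruptcy of loved ones as the examples.

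On timing, the section on the second phase describes random assignment, then consent and pre-test, then the sessions. Data collection tools and methods has the same order: "After the woman is randomized to the control or intervention group and has signed the written consent". Both events therefore follow allocation.

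On exposure to the attendance rule, the second-phase section delivers the intervention "during 6 sessions of 45–60 min once a week and for 6 weeks by a trained instructor". For controls it says "a one-hour session for the control group will be provided with the routine training of the above-mentioned centers". The Control group section describes the same arm differently: "The control group will continue to receive routine care, plus ongoing training on how to follow up sexually transmitted infections". It gives no number of sessions.

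The Sample size section allows for losses: "considering a drop-out rate of 10%, the sample size is set at 20 participants in each group". The Analysis section plans repeated-measures analysis of variance with Bonferroni comparisons and names no analysis population. The post-test is planned for both groups two months after the last intervention session.

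**The concern.** Randomisation makes the two groups comparable only if they stay as allocated. A rule that removes women for what happens after allocation can undo that, above all when it acts on one arm. If the women who miss sessions differ in PTSD course from those who attend, the retained intervention women are a selected group set against a control group not selected by attendance.

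A pre-post repeated-measures analysis of variance needs both scores, so a woman without a post-test contributes nothing to it. With 20 per arm, losing two to six women from one side could shift the PCL-5 contrast, raise the type I error and use up the drop-out allowance. Post-tests that are never taken cannot be recovered later by any analysis.

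**Working it through.** **1. The plan's own figures.** The SDs are 7.95 and 8.06, the difference 7.5, α = 0.05 (taken as two-sided) and β = 0.2.
- Pooled SD = √((7.95² + 8.06²)/2) = 8.005.
- n = 2 × [8.005 × (1.960 + 0.842)/7.5]² = 17.88, so 18 per group.
- 18/0.9 = 20 per group.

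Both stated figures reproduce. The allowance is two women per arm.

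**2. Who can meet the attendance rule.** With one session, P(missing 2 or more) = 0 at any absence rate. With six sessions and independent absences at rate p, it is 1 − (1 − p)⁶ − 6p(1 − p)⁵. The documents give no absence rate, so p is an assumption.

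| p per session | P(missing 2 or more of 6) | Expected, of 20 women |
|---|---|---|
| 5% | 3.3% | 0.7 |
| 10% | 11.4% | 2.3 |
| 15% | 22.4% | 4.5 |
| 20% | 34.5% | 6.9 |

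At 10% absence per session this rule alone uses up the two women allowed for in the intervention arm.

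**3. Possible bias in the planned contrast.** With two time points, the group-by-time test compares change scores. Assumptions, none of them from the documents except the rounded SD and the arm size:
- no true effect, 20 per arm, SD 8 at both times;
- baseline-post correlation 0.5, so the SD of change is 8 × √(2 × (1 − 0.5)) = 8;
- the k intervention women with the highest liability to be absent are removed;
- that liability correlates r_post = 0.3 to 0.5 with the two-month PCL-5, and r_base with baseline, from 0 up to the value of r_post.

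Spurious benefit = (r_post − r_base) × 8 × m. Here m is how far the mean of the retained women's liability falls below zero, in SD units.

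| Removed | m | Largest bias (r_post 0.5, r_base 0) | Range of bias | Highest type I error (simulated) |
|---|---|---|---|---|
| 2 (10%) | 0.18 | 0.5 × 8 × 0.18 = 0.7 | 0 to 0.7 | about 6% |
| 4 (20%) | 0.33 | 0.5 × 8 × 0.33 = 1.3 | 0 to 1.3 | about 8% |
| 6 (30%) | 0.48 | 0.5 × 8 × 0.48 = 1.9 | 0 to 1.9 | about 10.5% |

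The largest value is 1.9/7.5 = 25% of the target difference. If absence tracks only stable severity (r_base = r_post), the bias is about zero and the type I error stays near 5%. If it tracks worsening, the bias is at the top of the range. If absence were tied more closely to baseline than to the later score, the sign would reverse: at r_base 0.5, r_post 0.3 and six removed, (0.3 − 0.5) × 8 × 0.48 = −0.8.

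**4. Power at a 7.5-point difference (two-sided t-test, stated SDs).** Power is 82% at 20 v 20, 78% at 18 v 18, 75% at 16 v 18 and 72% at 14 v 18.

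**The case against.** Four stronger readings are tempting, and the documents do not carry them.

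- **The attendance rule can only ever act on the intervention arm.** This follows from the single control session in the second-phase section. The Control group section calls the training ongoing, and more than one control session would soften the claim. No such schedule is given, so the arithmetic stands for the one description that can be counted.
- **Excluded women are dropped from the analysis, so the groups compared are no longer the randomised ones.** The article never says so. It plans the post-test for both groups without an attendance condition, and analysis sets are often left to a full protocol or analysis plan, neither of which is shown. Still, exclusion with no statement of retention reads most naturally as removal. If exclusion ends follow-up, no analysis plan can supply the missing scores.
- **The bias favours the intervention.** Avoidance in PTSD makes this plausible, but women who recover early may also stop coming. A calculation on the post-test score alone would show the same maximum as above, but it would hide that much or all of the bias cancels in a change score when absence reflects stable severity.
- **Crises are detected more often in the intervention arm because it is seen weekly.** The article does not say how crises are ascertained, and the crisis rule can apply in either arm. Unequal detection is an inference.

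**Conclusion.** The point holds in this form. The only two exclusion criteria remove randomised women for later events. Under the one-session control description, the attendance rule falls on the intervention arm alone. Nothing in the article says that these women are still measured or analysed.

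The timing of the events and the session arithmetic are firm. Removal from the analysis is the natural reading and is not stated. The size and direction of any bias are not fixed by the documents: 0 to 0.7 points at the plan's own 10% loss and 0 to 1.9 at 30% are illustrations under the assumed correlations. The sample size calculation is not in error. The change is needed before follow-up is complete, because it concerns data that would otherwise not be collected.

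**What to change.** - Remove both items as grounds for exclusion from follow-up and from the analysis. Whether a woman continues the sessions is a separate clinical matter for the investigators.
- State that the two-month post-test is sought from every randomised woman, whatever her attendance or life events, and that all are analysed in the arm to which they were allocated.
- Record attendance and crises in both arms. Report women who attended at least five of the six sessions as a labelled secondary analysis.
- Reconcile the two descriptions of the control training, and state how many sessions it has.

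The cost is a change of wording and a few follow-up calls; the article already provides telephone contact for two months after the intervention. The estimate may be smaller than one restricted to attenders. If all 40 women are measured, power is 82%, against 78% at 18 per arm.
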